**Figure 1 fig1:**
[figure not shown]
The theoretical model for the intervention is based on a modified version of the theory of the planned behavior (TPB; Ajzen, 1985).

## Objectives

Using a full RCT design, the aim of this project is to develop and empirically test an intervention program targeting harassment and bullying as the main distal outcomes and helping behavior among bystanders as the main proximal outcome. While all occupational groups are potentially at risk for workplace harassment and bullying, some occupations are more exposed than others. Research in the Norwegian context (Einarsen and Raknes, 1997; Nielsen et al., 2012) as well as internationally (Baillien et al., 2011; Notelaers et al., 2011) has identified industry workers as a particularly risky group, and particularly so for low intensity bullying (Einarsen and Raknes, 1997). The intervention will therefore be conducted in a large Norwegian industrial organization that provides engineering, procurement, and construction services to the oil and gas industry. The oil and gas industry is a key driver for the Norwegian economy and knowledge about how reducing the occurrence of workplace harassment and bullying may therefore have important implications at the individual, organizational, and societal levels. This protocol will describe the trial design, participants, procedure, intervention program elements, randomization, ethical consideration, and statistical analysis that will be included in the project.

## The Intervention

This intervention is based on an existing workplace intervention developed by researchers and practitioners in Denmark, yet tailor-made for the public sector (Mikkelsen and Hogh, 2019). The intervention was customized to a Norwegian industrial setting by the authors, representing both researchers and practitioners. Consequently, the intervention described here is based on the structure of the original Danish intervention but is customized to a new sociocultural, industrial, and socioeconomic context. It should be noted that in accordance with the original intervention, a main overarching goal of this research is to develop an easy to use and standardized intervention which enable user-organizations to master the implementation themselves, and thereby not be dependent on professional and external consultants.

The workplace intervention, called “Grip inn” (“Intervene!”), is based on existing literature and empirical research on bystander behavior (e.g., Paull et al., 2012; Pouwelse et al., 2018; Ng et al., 2019). The main theoretical assumption behind the intervention is that the actions of bystanders in situations where coworkers are exposed to acts of bullying and harassment can either escalate or reduce workplace harassment and bullying. Hence, stimulating early, active and constructive intervention by bystanders should prevent further escalation and possibly create an anti-bullying climate. A flow-chart of the content of the intervention is shown in Figure 2 and will be described in the following.

**Figure 2 fig2:**
[figure not shown]
A description and flow-chart of the contents and main elements of the intervention.

The intervention comprises a preparatory part in order to anchor the program among managers, health and safety representatives, and labor union representatives. This initial preparatory part aims at increasing ownership to the program at all management levels and among elected health and safety representatives, and labor union representatives, thereby ensuring that key stakeholders contribute to successful implementation and follow up of the intervention.

The program is further divided into **three elements:**

1. A **planning meeting** at the workplace/department prior to the program with managers at the department level, the local labor union representative, the local health and safety representative, and a local HR representative.2. A 3-h **group session** with work-teams of 15–30 employees with their supervisors, managers, and elected health and safety representatives as participants.3. A **follow-up session** with department managers, those line managers, and elected health and safety representatives that participated in element two with the aim of following up ideas and suggestions for bystander guidelines created by employees in element two.

These three elements will now be described in more detail:

The first element consists of an initial meeting with the department manager and HR representatives laying the foundation for how to divide the department into groups used in the second part of the program and to prepare the department manager for his or her active role as host in the main intervention.

The second element and main part of the intervention, the group sessions, concentrates on the participants’ awareness of, knowledge about, and perceptions related to workplace bullying and harassment and of the possible role of bystanders. The main focus is on the opportunities for bystanders to intervene constructively in such situations. The sessions have a duration of 3 h and are divided into four consecutive parts with short breaks between each section.

1. An opening part is led by the department manager, starting with a 5-min video talk by the executive vice-president on the importance of the intervention to the company. Thereafter, the department manager provides a talk on the importance of the issue, providing also information about the organization’s policies and procedures for handling workplace bullying and its complaints and investigation procedures. Thereafter, the consultant leading the intervention has a 15–20-min presentation on the issue of workplace bullying and the role of bystanders and their possible role taken in a bullying scenario. This part is intended to last for 45 min.2. The second part is made up of two 10 min films describing two typical bullying scenarios, each followed by group discussions on the role of the bystanders in these films and how the bystanders intervened and could have intervened more constructively than they actually did. This part adds up to approximately 40 min.3. The third part includes a scenario quiz focusing on possible bullying and harassment situations asking how participants themselves think they would have handled the situation (by using an interactive presentation tool), followed by group discussions on how their work team usually reacts and should react to these different kinds of examples of bullying and harassment. This part is intended to last for 40 min.4. The last part consists of a group discussion with the aim of developing suggestions and norms for how one should react as a bystander and how one may intervene in specific situations with bullying and negative acts. Each group writes up their suggestions and ideas. This last part is intended to last for about 30 min, including a closing talk from the department manager of the way forward, the importance of the issue at stake, and his/her summation of the 3-h session.

The third element is a group session for line managers and a health and safety representative. The aim of this session is to develop local guidelines for the department on how bystanders could and should intervene when observing acts of bullying and harassment, based on the suggestions derived from the “Grip inn/Intervene!” group sessions. Lastly, an action plan for the implementation and follow up of these bystander guidelines are discussed and developed. The session will be led by the department manager and a consultant.

### Basic Principles in the “Grip Inn/Intervene!” Group Sessions

The “Grip inn/Intervene!” program is based on three pillars. A fundamental approach in all three pillars is participant involvement (Birzer, 2002). As a first pillar, scenario-based training will be introduced in order to increase bystander awareness, knowledge, and behavior. The second pillar will involve a scenario-based quiz that is developed in order to increase the knowledge of how bystander roles may relate to their own work context and to make the participants reflect on their own bystander behavior as well as the behavior of their work team. As the third pillar, the work teams develop suggestions for how bystanders should act, which is further developed into local guidelines in a collaboration including the manger and the local elected health and safety representative. This is done to ensure formal commitment and further enhancement of bystander intervening behavior and to engage and place the intervention within ongoing formal labor relations and health and safety system in the said organization.

Furthermore, the intervention assumes that upper management support and active involvement and ownership among department managers are crucial to success, hence role of the department manager and the executive vice president are vital in the planned intervention.

## Methods and Analysis

### Reference Group

In order to establish the intervention in the case company and to calibrate the perceptions of the research group with the actual working environment in the company, a reference group is set up to advice on the implementation of the project. The reference group is comprised of key stakeholders within the case company. The members were recruited by the HR department of the case company and include upper managers, first line managers, an occupational health representative, labor union representatives, and health and safety representatives.

### Study Design

This project has an RCT design that includes a range of departments from the case company, a Norwegian industry company. The company has two main locations, one on the west coast (location A) being the larger plant with some 1,600 employees and one in mid Norway (location B) being the smaller plant with some 800 employees. In location A, being the larger facility, all departments in the production part and two administrative departments will be randomly assigned to an intervention group and a control group. The control group will receive the intervention 6 months later, as will location B. As such, the location that is given the intervention last (location B) will also serve as an additional control group for the first interventions carried out in location A. Hence, we have two control groups for the initial intervention. In order to carry out a valid and reliable study of causal relationships and mechanisms, it is necessary to use a design where the study variables are measured repeatedly over time. In this project, we will use a mixed method design by combining a longitudinal survey, qualitative interviews, with this RCT design. All employees in the selected departments in the two locations of the case company will be invited to participate in a prospective questionnaire survey that will be distributed three times during a 12-month period. The questionnaire will be identical at all assessment points. It will be possible to distinguish between managers with personnel responsibility, managers without personnel responsibility, safety representatives, labor union representatives, other level employees, and the unit to which they belong. Data will be collected through *Surveyexact*, a web-based system for secure administration of questionnaires. The system is developed for the purpose of tracking individuals over time in a way that satisfies demands for anonymity and personal security and data protection. When accessing the web-based questionnaire by a link, the respondents will be asked to provide their informed consent before responding to the questionnaire. No personally identifiable information about respondents will be available to researchers, as data will be de-identified prior to analyses.

To obtain detailed information on how the intervention is perceived by the participants, qualitative interviews will be conducted with selected employees in different units/teams of the case company. Finally, immediately after the intervention, a short questionnaire and evaluation form focusing on satisfaction and perceived relevance of the intervention program will be sent out to all those who participate in the 3-h-group-sessions of the intervention.

### Sample

All employees in the intervention and control groups will be invited to participate in the three survey measurements. The total number of employees participating from both locations amounts to about 1,500. The surveys will be carried out approximately 4–6 months after intervention as well as 10–12 months, this to study the outcomes of the control groups who receive the intervention 6 months later and in order to study more long-term effects of the initial intervention.

Each employee in the company is provided with a smartphone when starting their employment. The survey will therefore be conducted electronically using these personal smartphones. The purpose of the survey will be to identify changes in the prevalence of bullying behavior, the social climate in the department, as well as the role played by bystanders in the working environment.

### Statistical Power

In order to estimate sample size, we conducted a power analysis. One of the primary goals of power analyses is to estimate the number of respondents required in a study to minimize the likelihood of a false negative finding. In the context of intervention studies, the goal is to estimate the number of respondents per group to detect a difference between intervention and control groups. An *a priori* power analysis was conducted using G*Power 3.1.9.2 (Heinrich-Heine-University, Dusseldorf, Germany) with an alpha level of 0.05, power established at 0.80, and an effect size of 0.279. The optimal sample size calculated turned out to be 204 in each sample group (control and intervention group), yielding an optimal total sample size of 408. Based on previous survey studies from Norway in similar settings, the expected response rate is 55–70% at each of the measurement times. For the baseline measurement, the expected response rate will provide a sample size in the area of 750–1,050 respondents. Across all three time points, such a response rate will provide a sample size of about 190–515 respondents. Thus, the intervention study will strive for meeting the high end of the expected response rate of similar studies to meet the estimate from the power analysis and should have no problem in meeting sample sized from T1 to T2. The survey will be conducted electronically. With a total of three assessments over 10–12 months, the time interval between the measurement times will be 4 months.

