## Abstract

**Background:** Workplace bullying is an important and prevalent risk factors for health impairment, reduced workability and lowered efficiency among both targets and observers. Development and tests of effective organizational intervention strategies are therefore highly important. The present study describes the background, design, and protocol of a cluster randomized controlled trial evaluating the effectiveness of an organization-wide intervention on preventing workplace bullying with a focus on promoting active and constructive bystander behavior. The main overarching goal is to develop an easy to use and standardized organizational intervention based on theory and research in the role of bystanders in bullying situations with the potential of reducing the prevalence of workplace bullying. The theoretical framework of the study is theory of planned behavior (TPB; Ajzen, 1991).

**Methods/Design:** Using a full randomized control trial (RCT) design, this project will empirically test the outcomes of an intervention program targeting bullying and harassment as the main distal outcomes and perceived behavioral control and helping behavior among bystanders as the main proximal outcome. A 1-year cluster randomized controlled design will be utilized, in which controls will also receive the intervention. About 1,500 workers from two different locations of a Norwegian industrial company will be randomized into one intervention group and two control groups with at least 400 workers in each group. A survey will be conducted electronically. With a total of three assessments over 10–12 months, the time interval between the measurement times will be 4 months. Thus, the data collection will take place at baseline, completion of the intervention and at 4 months follow-up.

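### The 204 per group for 80% power assumes individually randomised, independent workers, but the trial randomises departments, so the stated power does not hold

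*Protocol article*

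**What the plan says.** The Abstract describes the trial as clustered: "A 1-year cluster randomized controlled design will be utilized". Study Design makes the department at location A the unit of allocation: "all departments in the production part and two administrative departments will be randomly assigned to an intervention group and a control group". The main component of the programme is given to intact teams; The Intervention describes sessions for "work-teams of 15–30 employees with their supervisors, managers, and elected health and safety representatives as participants".

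The Statistical Power section reports a calculation in G*Power "with an alpha level of 0.05, power established at 0.80, and an effect size of 0.279". It concludes: "The optimal sample size calculated turned out to be 204 in each sample group (control and intervention group"), 408 in total. It then compares the expected number of respondents directly with that target and expects no difficulty in meeting it from T1 to T2. No ICC, cluster size, number of departments or design effect appears.

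Elsewhere, the multilevel model in Quantitative Data Analysis and Statistics names two levels only: measurements within individuals. Strengths and Limitations notes that the data would permit models at work-unit level, but does not connect this with the sample size.

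**The concern.** When departments are randomised, workers in the same department do not give independent information about the intervention effect. Correlation is to be expected here. The programme is delivered to whole teams, departments write their own bystander guidelines, and several outcomes (social climate, colleagues' norms, informal surveillance) describe a setting that respondents share. A sample size that treats workers as independent overstates the power.

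The 80% is the protocol's only justification of its size. If true power is well below it, a non-significant result says less about the programme than a reader relying on the 80% would suppose. Under Dissemination, the company will use the findings to decide on wider roll-out, so the error has a practical consequence.

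**Working it through.** **Inputs from the protocol article.** Alpha 0.05, power 0.80, effect size 0.279, 204 per group with equal allocation (Statistical Power); departments as the unit of randomisation (Study Design); session groups of 15–30 (The Intervention); at least 400 workers per group (Abstract); response of 55–70% per wave (Statistical Power).

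**Inputs assumed, because the protocol does not give them.** Respondents per cluster m = 15 to 50, ICC = 0.01 to 0.10, and, for the small-sample check, 5 or 10 departments per arm.

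**Step 1: reproduce the stated figure.** For two independent means, n per group = 2(1.960 + 0.842)²/d². With d = 0.279 this is 2 × 7.849/0.0778 = 201.7, so 202. The exact noncentral t calculation gives 203 (80.1% power), and 204 gives 80.3%. At d = 0.2785 it gives exactly 204, so the difference of one is rounding of d. A one-sided test would need 159 and does not fit. The 204 is thus the plain two-sided figure with no clustering allowance in it.

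**Step 2: add the design effect.** DEFF = 1 + (m − 1) × ICC. The number needed per group is 204 × DEFF, the effective number at 204 is 204/DEFF, and the detectable effect at 80% power is 0.279 × √DEFF. Power is Φ(0.279 × √(204/(2 × DEFF)) − 1.960).

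For m = 20:

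| ICC | DEFF | Needed per group | Power at 204 | Detectable d |
|---|---|---|---|---|
| 0.01 | 1.19 | 243 | 73% | 0.30 |
| 0.02 | 1.38 | 282 | 67% | 0.33 |
| 0.05 | 1.95 | 398 | 52% | 0.39 |
| 0.10 | 2.90 | 592 | 38% | 0.48 |

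Power at 204 per group for other cluster sizes:

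| m | ICC 0.01 | ICC 0.02 | ICC 0.05 | ICC 0.10 |
|---|---|---|---|---|
| 15 | 75% | 70% | 58% | 44% |
| 30 | 70% | 61% | 44% | 30% |
| 50 | 64% | 52% | 33% | 21% |

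**Step 3: few departments.** With a small number of clusters, the reference distribution is t on 2(J − 1) degrees of freedom, J being departments per arm. Spreading 204 over J = 10 (m = 20.4, 18 df) gives power of 68%, 62%, 48% and 34% at ICC 0.01, 0.02, 0.05 and 0.10. With J = 5 (m = 40.8, 8 df), ICC 0.02 gives about 46%.

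**Step 4: does the expected sample leave slack?** Treating response as independent between waves (an assumption, consistent with the upper three-wave figure of 515 ≈ 1,500 × 0.70³), a group of 400 yields:

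- at 70%: 400 × 0.70 = 280 at one wave, and 400 × 0.70² = 196 at both T1 and T2;
- at 55%: 220 at one wave, and 121 at both.

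The T1–T2 figures are below 204 before any design effect. Even 280 per group covers a DEFF of only 280/204 = 1.37, that is, an ICC of about 0.020 at m = 20 or 0.013 at m = 30.

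**The case against.** Four points can be made in the protocol's favour.

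1. **The size of the loss rests on assumption.** The protocol gives no ICC, number of departments or department size. Session groups are not the randomised unit, and 15–30 attendees at 55–70% response is only about 8–21 respondents. This stands: only the direction is certain. However, departments are divided into session groups, so a department is likely to be larger than one team, which makes the loss greater.

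2. **Baseline adjustment could recover power.** The hypotheses concern change from T1 to T2, and the analysis section says longitudinal associations will be adjusted for stability. With an assumed T1–T2 correlation of 0.6 and variance multiplied by 1 − 0.6² = 0.64, power at 204 per group and m = 20 becomes about 90%, 85%, 71% and 54% for the four ICCs. At low ICC the shortfall disappears. But the correlation is an assumption, the factor is approximate under clustering, and the power section claims no such credit.

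3. **The realised sample may exceed 204 per group.** Three groups of 500 at 70% response give 500 × 0.70² = 245 T1–T2 respondents per group, and 81% power at m = 20 and ICC 0.01. At ICC 0.02 this falls to 75%. At 55% response there are about 151 per group, with power below 80% even without clustering. Location B does not help the randomised comparison, since it is assigned as a whole site and adds no randomised departments.

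4. **The arithmetic is correct for the test used.** True. The fault is that the test does not match the design.

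These points limit how large the shortfall can be said to be. None makes the printed claim valid.

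**Conclusion.** The concern holds. The 204 per group is the sample size for an individually randomised trial, and with departments randomised any ICC above zero takes that test below 80%. That much needs no assumption about m or the size of the ICC.

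The size is conditional. For an unadjusted comparison at 204 per group, with m = 15–30 and ICC 0.01–0.05 assumed, power runs from about 75% down to 44%, and 233 to 500 per group would be needed. Few departments or larger departments lower it further; adjustment for T1 or a larger realised sample raises it. No single figure can be given as the trial's power, but the stated 80% is not supported for the design described.

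**What to change.** In Statistical Power, withdraw the statement that 204 per group gives 80% power, and the reassurance about T1–T2 numbers that depends on it. Replace them with power, or the minimum detectable effect, for the design as randomised:

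- state the number of departments per arm at location A and the expected respondents per department at T1 and T2;
- apply 1 + (m − 1) × ICC over a declared ICC range, with t-based inference suited to the number of departments;
- if credit is taken for T1 adjustment, state the assumed correlation and show results with and without it;
- re-estimate the ICC from the T1 survey and update the statement before outcomes are analysed.

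The cost is a rewritten paragraph and probably a less favourable power figure. The workforce is fixed, so no additional participants are required.

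### The expected-respondent ranges do not match the stated 55–70% response, and totals over three groups are set against a two-group requirement, so the T1–T2 assurance is unsupported for the randomised comparison of completers

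*Protocol article*

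**What the plan says.** The Statistical Power section bases its calculation on a comparison of two groups, "with an alpha level of 0.05, power established at 0.80, and an effect size of 0.279". It arrives at 204 per group, "yielding an optimal total sample size of 408".

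On response it says that "the expected response rate is 55–70% at each of the measurement times". At baseline this "will provide a sample size in the area of 750–1,050 respondents", and across all three time points "such a response rate will provide a sample size of about 190–515 respondents". It adds that the study will aim for the upper part of the response range in order to meet the power estimate, and "should have no problem in meeting sample sized from T1 to T2". It gives no respondent figure for T1–T2 and none per group.

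The base for these totals is the roughly 1,500 employees across both locations given under Sample. The Abstract divides them into "one intervention group and two control groups with at least 400 workers in each group". Under Study Design, only departments in location A are randomly assigned to intervention or control. Location B serves as an additional control group.

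**The concern.** One paragraph appears to use two different lower response rates: 55% in the text and 50% in the figures. It then compares respondents counted over three groups with a requirement for two. A reader who sets the pooled totals beside 408 would think the T1–T2 comparison comfortable, whereas the randomised comparison uses only part of that pool.

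This paragraph is the article's feasibility argument for its T1–T2 hypotheses. If the assurance does not carry over to the two randomised groups, the study may be less able to detect the planned effect than readers are told, and that is before any allowance for clustering by department.

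**Working it through.** **Inputs.** Alpha 0.05, power 0.80, effect size 0.279, 204 per group (408 in total), and response r of 55–70% per wave, all from Statistical Power. About 1,500 employees, from Sample. Three groups of at least 400, from the Abstract. Two randomised groups, both in location A, from Study Design.

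**1. The plan's requirement reproduces.** A two-sided two-sample t-test at a standardised difference of 0.279 needs 203 per group (202 by the normal approximation). Power at 204 per group is 0.803. The 204 stands.

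**2. The respondent ranges.** The upper ends show the method: 1,500 × r at baseline and 1,500 × r³ over three waves.

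| r | 1,500 × r | 1,500 × r² | 1,500 × r³ |
|---|---|---|---|
| 50% | 750 | 375 | 187.5 |
| 55% | 825 | 454 | 250 |
| 70% | 1,050 | 735 | 514.5 |

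The stated 1,050 and 515 follow from 70%. The stated 750 and about 190 follow from 50%. Using r³ treats response as independent between waves, which the article does not say.

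**3. Three groups against two.** The pooled T1–T2 count, 454–735, exceeds 408 at every stated rate, but it covers three groups. With at least 400 people in the third group, any two groups hold at most 1,500 − 400 = 1,100.

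Over three waves at 70%, 1,100 × 0.343 = 377, against 408. With equal thirds, 1,000 × 0.343 = 343. By the article's own method, then, even the top of the response range does not reach its own estimate for two groups.

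**4. T1–T2 completers per randomised group** (group size × r², with individual-level power at 0.279, two-sided 0.05). Group sizes are not stated beyond the minimum, so three are shown: the floor of 400, equal thirds of 500, and 550, which is the most that both randomised groups can have.

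| Group size | At 55% | Power | At 70% | Power | r needed for 204 |
|---|---|---|---|---|---|
| 400 | 121 | 0.58 | 196 | 0.79 | √(204/400) = 71.4% |
| 500 | 151 | 0.68 | 245 | 0.87 | √(204/500) = 63.9% |
| 550 | 166 | 0.72 | 270 | 0.90 | √(204/550) = 60.9% |

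At 55%, reaching 204 takes a group of 204/0.3025 ≈ 674. Two such groups would leave about 150 of the 1,500 for the third, below its minimum of 400. So at 55% at least one randomised group falls short under every allowed split.

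**5. Other ways of counting.** If all T2 respondents count, the smallest case is 400 × 0.55 = 220 per group, with power of about 0.83. If the same people answer both waves, completers reach at most 220–280 per group of 400 and 275–350 per group of 500. Pooling both controls (500 against 1,000) gives completers of 151 against 303 at 55%, with power of about 0.80, but that comparison leans on a location that was not randomised.

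**The case against.** The strongest reply is that 204 comes from an independent two-group test and so counts respondents per group, not people who answer twice. On that count every group meets 204 at each wave, even at 400 × 55% = 220. The multilevel analysis described under Quantitative Data Analysis and Statistics nests measurements within individuals and need not be limited to completers. This stands as a reason not to call the assurance wrong outright. Against it, the hypotheses concern change from T1 to T2, and the article's own three-wave figures count completers.

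Three further replies also stand in part. With groups of 500 or 550, completers reach 204 from about 64% or 61% response, and the same sentence speaks of aiming for the upper part of the range. The per-group figures above use independence between waves, which is the unfavourable side if the same people tend to respond. And the 50%/55% slip understates respondents, so it cannot be the source of the optimism.

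A reader might infer that the T1–T2 assurance is simply false for the randomised groups. The documents do not support that, because group sizes, the dependence of response between waves and the analysed set are not fixed tightly enough. A reader might also turn the three-wave counts into power for intervention versus control. That would not be valid: controls receive the intervention after T2, so the contrast no longer exists at T3.

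**Conclusion.** The concern holds in a limited form.

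- **Arithmetic.** The lower ends 750 and about 190 contradict the stated 55%, which gives 825 and about 250. The error is conservative.
- **Comparison.** Totals over three groups are set against a two-group requirement. At 70% the three-wave completers in any two groups are at most about 377, against 408. This is a check against the article's own benchmark, not a power figure for a test at T3.
- **T1–T2 assurance.** It is unsupported for completers in the randomised comparison. It becomes tenable if response is about 64% or more with groups of 500 (about 61% with 550), if response is positively correlated between waves, or if all available responses are analysed. With both randomised groups at the minimum of 400, independent response leaves completers at 196 or fewer throughout the stated range.

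These results assume 1,500 invited, at least 400 per group, and the same response rate in every group. The completer counts also assume independent response between waves. All power values are at individual level and make no allowance for clustering.

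**What to change.** In the Statistical Power section:

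1. Restate the ranges as 825–1,050 at baseline and about 250–515 over three waves, or change the stated rate to 50–70%.
2. Say that the multi-wave figures assume independent response between waves.
3. Give the expected T1–T2 respondents per group, with the planned group sizes.
4. Replace the assurance with the power or detectable effect for intervention versus the randomised location A control at those numbers, and say whether completers or all available responses are used.
5. Do not present three-wave counts as meeting an intervention-versus-control requirement.

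The cost is one rewritten paragraph, with no change to design or data collection. The lower ends of the ranges rise, while the statement about T1–T2 becomes more guarded.
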